### Assignment of interventions: blinding

**
Who will be blinded?
**

Participants, their family members, and study team members involved with intervention delivery (IC and yoga instructors) will be aware of participants’ assigned intervention during the trial. It is not possible to avoid bias arising due to this. RAs will complete baseline and three-month follow-up assessments, and they will not interact in any way with the intervention team. RAs will not be aware of the intervention allocation status. Participants and family members will be instructed not to disclose whether they are receiving the intervention to the RAs at the time of three-month follow-up assessment. Additionally, RAs will also remind participants not to reveal their group assignment to them so that they remain blind to the treatment allocation of participants.

Obstetricians will not be aware of the intervention allocation status, minimizing the risk of any change in their behavior while dealing with the participants.

The intervention team led by the IC and the outcome assessment team comprising of RAs will not have any interactions during the trial. They will work independently of each other in separate locations and will have no communication about trial participants and their intervention allocation status. During the training of RAs in the outcome assessment team, special emphasis will be given to explaining the equipoise between the two interventions.

We will monitor the risk of contamination at the level of the yoga instructors, intervention coordinator, and participants. Yoga instructors and the intervention coordinator will be requested to not share the information about Yoga-M
_2_ with pregnant women other than those enrolled in the intervention arm (Yoga-M
_2_). They will also ensure that participants in both the arms adhere to the group randomly allocated to them.

**
Procedure for unblinding if needed
**

In case there is any yoga-related adverse event, allocation of intervention group will be revealed to obstetrician.

### Data collection and management

**
Plans for assessment and collection of outcomes
**

Case Record Forms (CRF) will be used by RAs to collect data at baseline and at three-months follow-up assessment. Both the baseline and follow-up assessment will be completed in the antenatal clinic of the Pravara Institute of Medical Sciences. Pen and paper format will be used for data collection. Data will be converted into digital format by manual entry using
Microsoft Excel. Data will be stored as a CSV (comma-separated values) file. There will be a date and time stamp of the original data entry and any subsequent change to the document will be noted in an audit trail. Data related to the fidelity and quality of yoga intervention delivery will also be in paper form and similar process will be used to enter and store data as a CSV file. Digital voice recorders will be used to collect qualitative data. A document containing memos and field notes will be maintained. The audio data will be transcribed in Marathi and then translated in English for analysis. The data will be anonymized but linked with the trial ID.

For each data source, the CRC will perform the data, range, and consistency checks at weekly intervals. The CRC will resolve the queries promptly and will update the database and maintain the audit trail. Initially, separate databases will be used to store different types of data. Once the data collection is complete, each individual database will be locked, and these separate databases will be merged into a master. Passwords will be used by the CRC to protect the data. No member of the trial team will have access to these passwords.

**
Plans to promote participant retention and complete follow-up
**

At the baseline, participants will be informed about the three-month follow-up assessment and an interview will be scheduled coinciding with their antenatal check-up. A reminder phone call will be made one week prior to the follow-up assessment. A seven-day window period after the due date will be allowed to complete the assessment. In case the participants are unable to visit the antenatal clinic, a home-visit will be planned as per the convenience of the participant.

**
Data management
**

A Trial Master File containing all the essential documents will be maintained. Trial documentation will be maintained for seven years after the end of the trial. At the end of this period, data in paper format will be securely disposed and data in electronic format will not contain any identifiable information.

All CRFs and other documents related to the study will be stored securely in the Directorate of Research, PIMS. Password-protected servers will be used to store all electronic records. To ensure participant confidentiality, coded identification numbers will be used to identify participant data. Participant information in paper format will be securely stored in locked cabinets. Anonymized data will be used for analysis and for presenting results at conferences and in scientific journals.

**
Confidentiality
**

The identity and privacy of research participants will be protected. Any variable which may help to infer the identity of any participant, will be deleted from the database.

### Statistical methods

Statistical analyses will be conducted in
Stata version 14.2 by the trial statistician (ST). Descriptive statistics (means and standard deviations or proportions) of sociodemographic characteristics and outcome measures will be provided for all trial participants at baseline and three-months after enrollment; this will include means and standard deviations, or proportions, in the two arms, as appropriate. The primary analysis will be intention-to-treat. Binomial regression models will be used to estimate risk ratios and 95% confidence intervals for binary outcomes, while linear regression models will be used to estimate regression coefficients for continuous outcomes. Analyses of continuous outcomes will additionally adjust for the baseline value of that outcome and any imbalances of baseline values of key covariates.

**
Methods for additional analyses (e.g., subgroup analyses)
**

**
*Process evaluation analysis.*
** IDIs and Focus Group Discussions will be audio-recorded, and field notes will be taken. English interviews will be transcribed verbatim while the interviews conducted in Marathi will be transcribed and translated into English. Bilingual team members, fluent in English and Marathi will carry out back-translation checks. Qualitative data will be analyzed using framework analysis approach. An
*a priori* coding framework with a set of high-level themes will be developed. Lower order themes will be inductively derived from the data.
NVivo 9 software (QSR) will be used to code the data. Principal investigator will be primarily responsible for the data analysis and synthesis of the findings.

**
Methods in analysis to handle protocol non-adherence and any statistical methods to handle missing data
**

Complier Average Causal Effect (CACE) analysis will be carried out to assess the effect of receiving treatment as defined in the protocol. This will be done in three ways. Full compliance is defined as attendance at three or more of the first five sessions and at least four other sessions. The first type of analysis will involve fully compliant participants. In the second type of analysis, participants with any compliance (attendance at one yoga session or more) will be included. The third type of analysis will include the number of sessions attended in its continuous form. The extent and pattern of missing data for each outcome will be explored. Multiple imputation of missing values will be performed if there are more than 10% missing values at endpoint.

**
Plans to give access to the full protocol, participant level data and statistical code
**

The full protocol will be available on a dedicated website: 

[name]

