Assessment of acceptability of the intervention will also be done using a structured satisfaction survey and a qualitative study. In-Depth Interviews (IDIs) with all yoga instructors and enrolled participants will be completed. Semi-structured interviews will cover themes related to the delivery, content, comfort, and complexity of the intervention. We plan to enroll around 15 participants (10 from the intervention arm and 5 from the control arm), however, the sample size for the qualitative study will be determined by data saturation.

The description of measures which will be used to assess the preliminary efficacy of the intervention is given in
Table 3.

**Table 3. T3:** Measures to assess the preliminary efficacy.

Outcome	Measure	Time-point
Stress	Perceived Stress Scale (PSS)	Baseline and three-months post-randomization
Quality of Life	EuroQoL 5 Dimensions Score (EQ-5D-5L)	Baseline and three-months post-randomization
Immune Function	Wisconsin Upper Respiratory Symptom Severity Scale	Baseline and three-months post-randomization
Immune Function	Serum C-Reactive Protein	Baseline and three-months post-randomization
Injuries due to yoga	Self-report log	Every week for three-months post-randomization
Serious Adverse Events (SAE)	SAE report form	Baseline and three-months post-randomization

**
Perceived Stress Scale (PSS)
**

Perceived stress will be measured using 10-item version of the original scale
^
22
^. The items in this instrument assess how unpredictable, uncontrollable, and overloaded participants appraise the situations in their lives in last one month. PSS has been widely used in research studies across the globe and it has acceptable psychometric properties
^
23
^. In this study, we will use the Marathi version of the PSS which was translated from the English version using the World Health Organization (WHO) guidelines for the process of translation and adaption of instruments
^
24
^.

**
EuroQoL 5 Dimensions Score (EQ-5D-5L)
**

European Quality of Life Five Dimension (EQ-5D-5L) descriptive system will be used to measure Health related Quality of Life (HRQoL). A single utility score will be calculated using the value set/preference weights for Thailand as the Eq-5D value set for India is under development
^
25
^. Participants will also provide an overall evaluation of their health using a visual analogue scale (VAS). We will use the Marathi version of EQ-5D-5L with permission from the EuroQoL Group
^
26

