^. The EQ-5D has been validated in different parts of the world
^
27
^. 

**
Wisconsin Upper Respiratory Symptom Severity Scale (WURSS)
**

The incidence and severity of upper respiratory tract infections in the participants will be assessed using the
Wisconsin Upper Respiratory Symptom Survey (WURSS-21). This is a 21-item scale; 10 items assess symptoms, nine items assess functional impairments, and there is one item each to assess the overall severity and change. Responsiveness, reliability, convergence, and importance to patients of this scale have been validated
^
28
^. Participants will complete WURSS-21 at the end of each day in the study. We will use the Marathi version of WURSS with permission from the developers.

**
Serum C-Reactive Protein (CRP)
**

Serum CRP levels will be determined using fixed-point immune-rate method (VITROS 250/350/5, 1 FS/4600/XT 3400 Chemistry Systems and the VITROS 5600/XT 7600 Integrated Systems). The limit of detection for VITROS Chemistry Products CRP slides is 2.72 mg/L.

**
Self-report log
**

Participants in both arms will maintain a log to document any injuries/non-serious adverse events during the duration of the trial.

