### Sample size

We anticipate that the standardized effect size between the two arms will be small (0.2). Hence, we plan to recruit 25 pregnant women in each arm (total=50) based on the recommendations by Whitehead
*et al.*
^
29
^.

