### Oversight and monitoring

**
Composition of the coordinating centre and trial steering committee
**

The Trial Management Group (TMG) will coordinate the day-to-day implementation of the trial. The Trial Steering Committee (TSC) will provide the oversight for the trial. TMG will comprise of the principal investigator, the RAs, the IC, ST, a clinician, and a patient representative. It will meet every two weeks. The TSC will meet every four weeks. It will be headed by an independent chairperson and there will be four other members. There will be representatives of the TMG on the TSC.

**
Composition of the data monitoring committee, its role and reporting structure
**

Due to the nature of the trial and low risk for participants, the TSC will also take on the role of the data monitoring committee. During the TSC meetings, data related to progress of the trial and safety of participants will be reviewed and discussed.

**
Adverse event reporting and harms
**

Previous evidence suggests that yoga during pregnancy is safe
^
30
^ and no adverse events have been reported in an earlier trial by Satyapriya
*et al.*
^
19
^. Records of all Serious Adverse Events (SAEs) will be maintained in a log by the CRC.

1) Death due to any cause2) Hospitalization due to any cause3) Suicide attempt4) Spontaneous abortion or stillbirth

SAEs in both arms will be documented by the RAs at three-month follow-up assessment. The IC and yoga instructors will also be trained to identify SAEs and notify them to the CRC. Within two weeks of becoming aware of any SAE (related or unexpected), the Institutional Ethics Committee will be informed about the same by PI. A standard operating procedure will include all the details pertaining to the detection, appropriate response and reporting of SAEs. If any SAE requires an immediate response, an independent medical specialist will do so within two working days. The criteria for unblinding of adverse events will be set
*a priori*. A summary of all adverse events will be sent to the Institutional Ethics Committee, the funder, and the TSC regularly as part of the progress report.

All necessary and appropriate medical assistance will be provided to participants in the PIMS for injuries related to participation in the trial (intervention arm). There will be no financial burden on the participants for trial related injuries and adverse events.

**
Frequency and plans for auditing trial conduct
**

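### The only comparative model named for binary outcomes, a binomial-regression risk ratio, suits rare harms badly with 25 women per arm

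*Protocol article*

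**What the plan says.** The Statistical methods section of the protocol article gives one sentence on modelling. For binary outcomes it reads "Binomial regression models will be used to estimate risk ratios and 95% confidence intervals for binary outcomes"; continuous outcomes go to linear regression. The same section plans means or proportions of the outcome measures by arm, with no interval attached to the proportions.

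Table 3 lists the outcome measures. Besides the stress, quality-of-life, respiratory-symptom and CRP measures, it has a row "Injuries due to yoga", taken from a weekly self-report log, and a row for SAEs, taken from the "SAE report form". On the log, the text below the table says "Participants in both arms will maintain a log to document any injuries/non-serious adverse events during the duration of the trial". Under Adverse event reporting and harms, SAEs are documented in both arms and include hospitalization for any cause.

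The Sample size section sets 25 women per arm. Oversight and monitoring justifies its committee arrangement with "Due to the nature of the trial and low risk for participants" and states that "no adverse events have been reported in an earlier trial". The Interventions section gives that trial's size as 51 yoga and 45 control women. No expected rate of SAEs or injuries is stated anywhere.

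**The concern.** A risk ratio from a log-link binomial model needs events in both arms. If one arm has none, the estimated log risk ratio runs off to plus or minus infinity and its Wald standard error becomes meaningless. If neither arm has any, the ratio is undefined. The protocol describes a low-risk intervention in two arms of 25, which is the setting where empty arms are common.

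What is at stake is the safety message of the pilot. The protocol intends to seek funding for a larger trial in pregnant women if delivery is feasible and acceptable. A ratio that cannot be estimated, or one with an enormous interval, is easily passed over as showing no difference in harms. An absolute estimate would show how little 25 women per arm can exclude.

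**Working it through.** **Inputs.** From the protocol: n = 25 per arm (Sample size); risk ratio by binomial regression with a 95% interval (Statistical methods); no adverse events reported in an earlier trial of 51 + 45 = 96 women (Oversight and monitoring; Interventions). Assumed, because the protocol gives no figure: a risk p of at least one event per woman over three months, equal in both arms, from 1% to 20%.

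**The plan's own figure.** The 25 per arm comes from a cited pilot recommendation for a standardized effect of 0.2. No alpha, power or formula is given, so it cannot be re-derived. It is a pilot rule on a continuous scale and says nothing about binary outcomes.

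**Step 1: chance of an empty arm.** One arm has no events with probability q = (1 − p)^25. At least one of two arms is empty with probability 1 − (1 − q)², and both are with probability q².

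| p | q | at least one arm empty | both empty |
|---|---|---|---|
| 1% | 0.778 | 95% | 61% |
| 2% | 0.603 | 84% | 36% |
| 5% | 0.277 | 48% | 8% |
| 10% | 0.072 | 14% | 0.5% |
| 20% | 0.004 | 0.8% | <0.1% |

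The chance exceeds one half only if p is below about 4.8%.

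**Step 2: an anchor from the protocol.** If the earlier trial is taken as 0 events in 96 women, the one-sided 95% upper bound is 1 − 0.05^(1/96) = 3.1%. At or below that rate the chance of an empty arm is at least 71%. This anchor is weak: that trial's event definition is not given and may not match the SAE list here.

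**Step 3: what the model returns.** Log-link binomial fits to tables with 25 per arm (first count yoga, second control):

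- 2 v 0: log risk ratio about 20.9, SE about 14,500, Wald interval 0 to infinity.
- 0 v 0: SE about 34,000, Wald interval 0 to infinity.
- 2 v 1: risk ratio 2.0 (0.19 to 20.7), so the model works once both arms have an event, though imprecisely.

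**Step 4: what absolute measures return.** The exact (Clopper-Pearson) two-sided 95% upper limit for 0/25 is 1 − 0.025^(1/25) = 13.7%. Newcombe 95% intervals for the risk difference, in percentage points, are −13.3 to +13.3 for 0 v 0, −9.7 to +19.5 for 1 v 0, −6.5 to +25.0 for 2 v 0, and −12.6 to +21.3 for 2 v 1. All are finite.

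**Step 5: follow-up completion.** This is the other clearly binary two-arm measure. At 25/25 v 22/25 the fit gives 1.14 (0.98 to 1.31), and at 24/25 v 22/25 it gives 1.09 (0.92 to 1.29). The standard error collapses only when both arms are fully complete. That has probability 0.95^50 = 7.7% at 95% retention and 0.90^50 = 0.5% at 90%.

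**The case against.** **The protocol never says that harms will be analysed by this model.** This is correct. The modelling sentence is generic, and it has other possible targets: follow-up completion, and perhaps the incidence of respiratory infection, which the article says WURSS-21 will assess. Applying it to harms is an inference. It is the natural one, since SAEs and injuries are listed outcomes recorded in both arms and no other comparative method is named.

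**The failure depends on a rate nobody has stated.** This also stands. SAEs include any-cause hospitalization, and the log takes any injury or non-serious event, so rates of 10% or more are possible. The risk ratio would then usually be estimable. A reader might infer that the safety analysis is bound to fail; the documents do not support that.

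**The interval from 0 to infinity is a Wald artefact.** This stands in part. A profile-likelihood interval from the same model is bounded on one side when a single arm is empty; for 0/25 v 2/25 its upper limit is about 1.5. The protocol does not specify the interval type. With both arms empty no method helps the ratio.

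**Proportions by arm are already planned, and a sparse-data fallback may sit in an analysis plan that is not shown.** The planned proportions do limit the harm: the data will be visible. But they carry no interval. The point also does not rest on a missing fallback. The scale and model are already stated here, and they suit rare events badly at this size.

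**A reader might extend the criticism to follow-up completion**, on the ground that an arm at 100% breaks the model. It does not: the ratio stays finite with one complete arm.

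**Conclusion.** The concern holds in a limited, conditional form. The one comparative method stated for binary outcomes is a poor choice for SAEs and injuries at 25 per arm if harms are as rare as the protocol suggests. At assumed equal rates of 5% or less per arm, about half to 95% of such trials would have at least one empty arm, and so no usable Wald risk ratio. At 10% the share is 14%, and at 20% under 1%. This rests on reading the modelling sentence as covering harms and on rates that are assumptions.

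It does not show that the safety data would be lost, because counts and proportions remain available. It does not extend to follow-up completion. It is worth correcting before analysis, but it does not threaten the trial's feasibility aims.

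**What to change.** In Statistical methods, add that for SAEs and for injuries or non-serious events the analysis is:

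- the number and proportion of women with at least one event in each arm, with exact (Clopper-Pearson) 95% intervals;
- the between-arm risk difference, with a Newcombe or exact unconditional 95% interval;
- a risk ratio only as a secondary measure, when both arms have events.

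Report the upper confidence limits, and do not read the absence of a significant difference as evidence of safety. The binomial risk ratio can stay for follow-up completion, and for respiratory infection incidence if that is analysed as a binary outcome.

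The cost is one sentence. The data are already to be collected, and no clinical procedure changes. The price is a wider and less favourable safety statement, since the absolute limits will be shown.

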### Oversight and monitoring

**
Composition of the coordinating centre and trial steering committee
**

The Trial Management Group (TMG) will coordinate the day-to-day implementation of the trial. The Trial Steering Committee (TSC) will provide the oversight for the trial. TMG will comprise of the principal investigator, the RAs, the IC, ST, a clinician, and a patient representative. It will meet every two weeks. The TSC will meet every four weeks. It will be headed by an independent chairperson and there will be four other members. There will be representatives of the TMG on the TSC.

**
Composition of the data monitoring committee, its role and reporting structure
**

Due to the nature of the trial and low risk for participants, the TSC will also take on the role of the data monitoring committee. During the TSC meetings, data related to progress of the trial and safety of participants will be reviewed and discussed.

**
Adverse event reporting and harms
**

Previous evidence suggests that yoga during pregnancy is safe
^
30
^ and no adverse events have been reported in an earlier trial by Satyapriya
*et al.*
^
19
^. Records of all Serious Adverse Events (SAEs) will be maintained in a log by the CRC.

1) Death due to any cause2) Hospitalization due to any cause3) Suicide attempt4) Spontaneous abortion or stillbirth

SAEs in both arms will be documented by the RAs at three-month follow-up assessment. The IC and yoga instructors will also be trained to identify SAEs and notify them to the CRC. Within two weeks of becoming aware of any SAE (related or unexpected), the Institutional Ethics Committee will be informed about the same by PI. A standard operating procedure will include all the details pertaining to the detection, appropriate response and reporting of SAEs. If any SAE requires an immediate response, an independent medical specialist will do so within two working days. The criteria for unblinding of adverse events will be set
*a priori*. A summary of all adverse events will be sent to the Institutional Ethics Committee, the funder, and the TSC regularly as part of the progress report.

All necessary and appropriate medical assistance will be provided to participants in the PIMS for injuries related to participation in the trial (intervention arm). There will be no financial burden on the participants for trial related injuries and adverse events.

**
Frequency and plans for auditing trial conduct
**

The sponsor and the Institutional Ethics Committee will monitor the aspects of the study on an ongoing basis.

**
Plans for communicating important protocol amendments to relevant parties (e.g., trial participants, ethical committees)
**

Approval from the TSC and the sponsor will be obtained for any modifications in the protocol that will affect the scientific aspects of the study, participant safety, scientific value of the study, or the way in which study is conducted. These modifications will be submitted to the Institutional Ethics Committee as amendments to the protocol. Changes made to the protocol will be communicated to the trial participants through written communication. The Final report submitted to the funder will enlist all the amendments to protocol.

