### Objectives

The overall aim of this pilot randomized controlled trial is to examine the feasibility, acceptability, and preliminary efficacy of a
**Yoga**-based intervention to improve maternal
**M**ental health and i
**M**munity (Yoga-M
_2_).

The primary objectives of this randomized pilot trial are:

1. To estimate participant eligibility, recruitment and retention-in-care and study completion rates.

2. To assess the feasibility of delivering Yoga-M
_2 _and acceptability of this intervention by the participants.

3. To assess the preliminary efficacy of Yoga-M
_2 _to improve maternal mental health and immune function.

**
Trial design
**

Single-blind individual randomized parallel group-controlled pilot trial with 1:1 allocation ratio.

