### Informed consent

A participant information sheet will be given to all eligible participants. The information sheet will include the details about the purpose of the trial, various study procedures, and contact details of the Principal Investigator and the Member Secretary of the Institutional Ethics Committee. An audio-visual version of this participant information sheet will be uploaded on the project
website and the participants will be informed about how to access this. Sufficient time will be given to participants to read the information sheet and to ask any questions about the trial. They will be then invited to participate in the study. 

Eligible participants who agree to participate in the study will provide informed written consent by completing a hard copy of the consent form (see
*Extended data*
^
17,
18
^). Prior to signing the consent form, participants will have opportunity to review the form and ask questions about the study. Participants who are illiterate (not able to read and write Marathi, but can communicate in Marathi), will provide a verbal consent (audio-recorded) after the RA reads out the information sheet to them. An impartial third party (a family member or a health care worker) will witness the consent process and will sign the consent form.

A separate written informed consent will also be obtained at three-month follow-up assessment, for the qualitative study and for the recording (audio/video) of yoga sessions to assess fidelity and quality of intervention delivery.

RAs will be trained to ensure that the purpose of the study, randomization and other study procedures are adequately explained, and the informed consent is appropriately obtained. They will be required to sign the consent forms as well.

A copy of the participant information sheet and the informed consent form will be handed over to the participants. Those who decline to participate will be asked the reason for refusal and with their permission, their age, education, occupation, and religion will be recorded. Refusals at three-month follow-up will also be recorded.

**
Additional consent provisions for collection and use of participant data and biological specimens
**

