### Assignment of interventions: allocation

**
Sequence generation
**

An independent statistician will generate randomization list using the statistical program
R (version 3.6.1). First, a list of variable block sizes (randomly selected block sizes of 2/4/6/8) will be created followed by a list of intervention allocation (Yoga-M
_2_ or EUC) using a 1:1 allocation ratio. The list will be shared with the Clinical Research Coordinator (CRC) based in the Directorate of Research, PIMS. They will prepare serially numbered, opaque, sealed envelopes using the randomization list.

**
Concealment mechanism
**

Participants will be randomly allocated to the intervention group by the IC using serially numbered, opaque sealed envelopes after they complete their baseline assessment.

**
Implementation
**

The IC will collect a set of opaque sealed envelopes from CRC as per the serial numbers, a few hours prior to the recruitment. The IC will open the opaque sealed envelopes (as per the serial numbers) in front of the participants and immediately inform them about the intervention group (i.e., Yoga-M
_2_ or EUC) they have been assigned to. Participants will be requested to not reveal their group assignment to the RAs at the three-month follow-up assessment. To maintain allocation concealment, neither the RAs nor any staff working at the hospital will have access to the randomization lists. The IC will inform the CRC the unique identification number of the participant (and no other details) and the intervention allocation group. The CRC will maintain the record of intervention allocation.

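### The Trial Management Group's membership contradicts the rule separating outcome assessors from the intervention team, and yoga-recording consent is set at the outcome visit, so assessor blinding is not protected as written

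*Protocol article*

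**What the plan says.** The design is labelled "Single-blind individual randomized parallel group-controlled pilot trial with 1:1 allocation ratio" (Protocol article, Objectives). Under Assignment of interventions: blinding, women, their families and "study team members involved with intervention delivery (IC and yoga instructors) will be aware of" the assigned arm. The RAs and the obstetricians are the parties to be kept unaware.

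The same section states how the RAs are to stay masked: "RAs will complete baseline and three-month follow-up assessments, and they will not interact in any way with the intervention team". It repeats the rule for the two teams: "The intervention team led by the IC and the outcome assessment team comprising of RAs will not have any interactions during the trial". It adds that they work in separate places and do not exchange information about individual women or their arms. The Recruitment section also has the IC working independently of the RAs.

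Oversight and monitoring sets up a Trial Management Group (TMG) to run the trial from day to day: "TMG will comprise of the principal investigator, the RAs, the IC, ST, a clinician, and a patient representative. It will meet every two weeks". No closed or split session is described. TMG representatives also sit on the Trial Steering Committee (TSC), which doubles as the data monitoring committee and reviews progress and safety data.

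Informed consent says: "A separate written informed consent will also be obtained at three-month follow-up assessment, for the qualitative study and for the recording (audio/video) of yoga sessions". The recordings are meant for assessing fidelity and quality of delivery. The next paragraph describes RAs as trained in obtaining consent and as signing the forms. The allocation section, meanwhile, asks women not to tell the RAs their group at the three-month visit.

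**The concern.** The protocol accepts that bias from the women's own knowledge of their arm cannot be avoided. RA masking is then the main protection left for the questionnaires that the RAs administer, and it is what the single-blind label rests on in the assessment of outcomes. The protocol secures it by complete separation of the two teams, then sets up a management group that removes that separation. The consent procedure places a question specific to one arm at the visit where the outcomes are collected.

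Two things are at stake: the credibility of the preliminary efficacy estimates for stress and quality of life, and the usability of the fidelity recordings if consent for them comes after the sessions have been held.

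**Working it through.** There is no planned figure to reproduce. The check sets the sections side by side.

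**1. Separation rule against TMG membership.** The blinding section forbids any interaction between the RAs and the IC-led team for the whole trial. The oversight section makes the RAs and the IC members of one group that meets every two weeks. A meeting attended by both is an interaction, so the two sections cannot both be followed.

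**2. What a joint meeting could disclose.** The IC keeps the intervention delivery logs, coordinates attendance at the weekly sessions, and acts when a woman misses two in a row (Outcomes; Strategies to improve adherence). These are day-to-day matters, and weekly sessions exist only in the Yoga-M2 arm. The trial plans 50 women from four neighbouring villages, so mention of one woman's attendance would identify her arm.

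**3. How often the occasion arises.** Taking three months as about 13 weeks, 13 / 2 = 6.5, or six to seven meetings in each woman's follow-up. With the seven-day visit window, 14 / 2 = 7. This counts meetings, not disclosures.

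**4. Recording consent and masking.** The RAs carry out the three-month assessment. Only Yoga-M2 women have sessions that could be recorded. A request for this consent in front of the RA, before the scales are complete, would show the arm at the visit where women are asked to conceal it.

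**5. Recording consent and timing.** Sessions run for 12 weeks, and the visit is due about 13 weeks after randomization. If sessions start soon after randomization, consent is sought about 13 − 12 = 1 week after they end. A later start would leave at most a few sessions, and the initial five-day teaching block would be long past. This problem stands whoever takes the consent.

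**6. Outcomes exposed.** PSS and EQ-5D-5L are collected by the RAs and are the most open to interviewer influence. Serum CRP is a laboratory assay. WURSS-21 is described as completed by the woman herself each day. Recruitment, attendance and retention come from logs.

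**The case against.** The best defence is that shared membership does not equal unblinding. The oversight section does not say that the TMG sees attendance or allocation for individual women. The narrower bar on exchanging information about women and their arms could be kept in a joint meeting, and split agendas may be set out in the full protocol. This stands against any claim that masking has failed. It does not remove the contradiction, because the broader rule of no interaction is also stated, and is the one breached.

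On consent, the text does not say who takes the separate form, whether it comes before or after the scales, or whether women in both arms receive the same form. The qualitative study draws on both arms, so consent for that part alone need not reveal the arm. This also stands: the unmasking is possible, not certain. The timing problem remains.

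On impact, this is a pilot, and the decision to go further rests on feasibility and acceptability. With 25 women per arm, the standard error of a standardized difference is about √(2/25) = 0.28 (unadjusted, complete data), so sampling error is large in any case. That limits the consequence but is no reason to leave two sections in conflict.

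Some stronger readings are tempting and should be resisted:

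- **The Clinical Research Coordinator (CRC).** Of this role the protocol says "The CRC will maintain the record of intervention allocation" and also "The CRC will resolve the queries promptly and will update the database and maintain the audit trail". A reader might see a further breach. But the CRC is nowhere declared blinded, does not assess outcomes and is not a listed TMG member, and changes leave an audit trail. Masking arm in the database would not help either, since the IC reports each identification number and arm to the CRC.
- **Home visits as a marker of arm.** These are also planned in either arm for women who cannot attend the follow-up assessment.
- **RA masking as the sole bias control.** RAs are also trained on equipoise between the arms.

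**Conclusion.** The point holds as a contradiction between two stated rules, together with a mistimed consent. The separation on which assessor blinding rests cannot be kept with the TMG as constituted. The recording consent can disclose the arm at the outcome visit and comes too late for its purpose. RA masking is therefore not protected as written.

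A reader might infer that blinding fails outright, or that every Yoga-M2 woman asked is unmasked to the RA. The documents do not support this, because they leave open what the TMG discusses and who takes the consent and when. Nor do they allow a size to be put on any interviewer bias.

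The size that can be stated is six to seven joint meetings per woman's follow-up, with exposure mainly of PSS and EQ-5D-5L. This assumes that the RAs and the IC usually attend and that three months is about 13 weeks. CRP and the feasibility logs are little affected.

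**What to change.** 1. Hold TMG meetings in split sessions. The RAs should not attend with the IC, or when intervention delivery (attendance, missed sessions) is discussed; the investigator relays data-collection issues. Keep RAs out of the TSC's data-review items. Amend the oversight section so that it agrees with the blinding section.
2. Move consent for session recording to just after allocation, taken by the IC before the first session.
3. Take consent for the qualitative interview only after the outcome scales are complete.

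The cost is revised wording and an ethics notification, with TSC and sponsor approval where the protocol's own amendment rule applies. No extra staff are needed, since the IC already meets each woman alone at allocation. The downside is that the RAs lose direct attendance at part of the meetings. The changes are best made before recruitment, because an assessor cannot be re-masked and consent given after a session cannot cover its recording in advance.
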